### Randomization and allocation

Block randomization with a block length of four will be employed. For each block, enrolled participants will undergo 1:1 randomization into the continuing-ETV therapy group and the switch-TDF therapy group. Randomization numbers will be generated using STATA/SE 15.1 and sealed in envelopes.

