## Abstract

**Background:**

Antiviral therapy has been reported to be associated with lower recurrence rate of hepatocellular carcinoma (HCC) for patients with hepatitis B virus (HBV) infection. While entecavir (ETV) and tenofovir disoproxil fumarate (TDF) were both recommended as first-line therapies for HBV patients, recent retrospective studies proposed a lower incidence rate of HCC occurrence or recurrence in those receiving TDF compared ETV. However, the survival benefits of switching to TDF therapy after prolonged ETV treatment before surgery remain uncertain. We delineate the rationale and design of SWITE, a randomized, open-label, phase III trial contrasting TDF switch therapy versus ETV maintenance in HBV-related HCC patients.

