### Follow-up

Patient follow-up begins post-hospital discharge. Visits to the surgical team will occur every 3 months during the first 3 years post-surgery. Check-ups, including CT and/or MRI, ultrasound, routine blood tests, liver and kidney function assessments, AFP, PIVKA, and HBV DNA level measurements, will be conducted at each visit (Table 1).

**Table 1 Tab1:** Participant timeline

	Study period												
	Enrollment/allocation	Post-allocation											Close-out
Timepoint	Pre-allocation	0 months	1 month	3 months	6 months	9 months	12 months	15 months	18 months	21 months	24 months	30 months	36 months
**Informed consent:**	×												
**Eligibility screen**	×												
**CT or MRI**	×												
**Laboratory test**	×												
**Allocation**	×												
**Surgery**		×											

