### Data collection and management

Investigators and coordinators will receive specialized training for data collection. All trial-related data will be recorded on study-specific CRFs. In particular, plenty factors, including different stages of cirrhosis, would play an important role in survival of patients with HCC after surgery. Comprehensive clinical data, including Ishak score of the resected specimen, fibrosis-4 index, aminotransferase-to-platelet ratio index, and other parameters for liver cirrhosis to evaluate the baseline stage of cirrhosis, will be prospectively collected. Besides, the death from decompensation of cirrhosis, HCC recurrence, and other reasons will be precisely recorded and recognized during the follow-up since decompensation in patients with cirrhosis is a competing event from HCC recurrence. Baseline assessments will be conducted pre-randomization, and missing data will be stored until received or confirmed as unavailable. Personal information will remain confidential. Data will be entered into Excel by two independent collectors, using participant numbers for identification. Access to information will be restricted. A data manager will oversee routine accuracy checks and address any issues with the investigators. Hard copy documents will be stored securely, and electronic files will have password protection. All documents will be saved for at least 5 years post-publication, with original data available upon request to the principal investigator.

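### Fixed, disclosed blocks of four make about a third of assignments deducible in this open-label single-centre trial, and the text is inconsistent on whether allocation precedes surgery

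*Protocol article*

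**What the plan says.** On the method of assignment, the section Randomization and allocation states "Block randomization with a block length of four will be employed" and "For each block, enrolled participants will undergo 1:1 randomization into the continuing-ETV therapy group and the switch-TDF therapy group". It adds "Randomization numbers will be generated using STATA/SE 15.1 and sealed in envelopes". No stratification is mentioned. The Abstract describes "a randomized, open-label, phase III trial contrasting TDF switch therapy versus ETV maintenance in HBV-related HCC patients", and both the Abstract and Study design give a single centre.

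On the timing of assignment, the statements are spread over several sections:
- Table 1 ("Participant timeline", under Follow-up) marks allocation in the column before time zero. It marks surgery at 0 months, under the post-allocation heading.
- Data collection and management says "Baseline assessments will be conducted pre-randomization". The same paragraph lists "Ishak score of the resected specimen" among the measures of baseline cirrhosis stage.
- The Methods paragraph of the Abstract mentions surgery at the end of its sentence on randomisation. It can be read as randomising after surgery, or as giving the randomised therapy after surgery.
- Inclusion criterion 3 requires curative resection or ablation.
- Exclusion criteria and Statistical analysis both commit to intention-to-treat (ITT) analysis.

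**The concern.** Sealed envelopes hide the next assignment, but they do not hide what the earlier assignments in the block imply. With one site, no blinding and apparently one running list, the same team can see every previous assignment. If the block length is known, the end of each block is predictable. Anyone who can foresee the next arm can, deliberately or not, bring a patient forward, hold one back or read an eligibility item more strictly. Randomisation then no longer protects the comparison of recurrence-free survival against differences in prognosis at entry.

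The timing adds to this. If allocation comes before the operation, a patient can be randomised before it is known whether the treatment was curative, and the arm may be known to those who operate. Removing patients who then fail the criterion departs from ITT. Keeping them brings in patients for whom recurrence after curative treatment is poorly defined. Because the switch is postoperative, no gain from early allocation is apparent in the text.

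**Working it through.** **Number of assignments.** The Sample size section gives 70% v 85%, one-sided alpha 0.05 and 80% power. Per arm, with pooled proportion 0.775:

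n = [1.645 × √(2 × 0.775 × 0.225) + 0.842 × √(0.70 × 0.30 + 0.85 × 0.15)]² / 0.15² = 94.8, rounded up to 95.

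That is 190 in total, and 190 / (1 − 0.20) = 237.5, rounded up to 238. Both stated figures reproduce. The article gives no figure for predictability, so there is none to compare with.

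**Predictability with a fixed block of four, 1:1.** Assume an observer who knows the block length and all earlier assignments. The six possible sequences are equally likely.

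| Position in block | Probability that it is fully determined | Probability that the best guess is right |
|---|---|---|
| 1 | 0 | 1/2 |
| 2 | 0 | 2/3 |
| 3 | 1/3 (first two alike) | 1/3 × 1 + 2/3 × 1/2 = 2/3 |
| 4 | 1 | 1 |
| Sum | 4/3 | 17/6 |

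- Known with certainty: (4/3) / 4 = 33.3%.
- Best guess correct: (17/6) / 4 = 17/24 = 70.8%.
- For 238 patients there are 59 full blocks plus two further assignments. Certain: 59 × 4/3 = 78.7, about 79. Correct guesses: 59 × 17/6 + 1/2 + 2/3 = 168.3, against 119 at 50%.

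**What varying the block size achieves.** This was simulated (300 runs of 238 patients) with an observer who knows the set of sizes but not which size is in use.

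| Scheme | Known with certainty | Best guess correct |
|---|---|---|
| Fixed 4 (exact) | 33.3% | 70.8% |
| Random 4/6 | 5.5% | 69.3% |
| Random 4/6/8 | 2.3% | 68.0% |

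Varying sizes remove most of the certain knowledge but little of the guessing advantage. That is why custody of the list and irrevocable registration belong in the fix.

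**Timing, side by side.**
- Table 1 has allocation first, then surgery.
- Data collection and management has baseline first, then randomisation. One baseline item needs a resected specimen, so for that item the order would be surgery, then randomisation. This contradicts Table 1.
- The Abstract sentence fits either order.
- The curative criterion can be planned before the procedure, but it is confirmed only at or after it.

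**Patients who fail the criterion after allocation.** The document gives no rate. Assumed range: 1% × 238 = 2.4 and 10% × 238 = 23.8, so about 2 to 24 patients.

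**The case against.** Several counter-arguments carry weight.

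- **Envelope handling.** Who holds the list, and whether envelopes are opaque and numbered, is detail that an article may leave to the full protocol. This stands, and its absence is not held against the plan. It does not answer the predictability point, which follows from the block length as stated.
- **Knowledge assumed.** The article does not say that recruiters know the block length or track assignments. This also stands: 33% and 71% describe what the design permits, not what has happened.
- **Limited remedy.** A reader might infer that varying the blocks brings guessing back to 50%. It does not; with 4/6/8 the figure is about 68%.
- **Eligibility.** A reader might infer that some assigned patients are bound to be ineligible. The documents do not show this. Screening covers patients scheduled for hepatectomy, and the curative criterion can be read as planned treatment. The most that can be said is that some may fail it later. Nor would benign histology by itself breach eligibility, because HCC is diagnosed by clinical criteria.
- **Endpoints.** A reader might infer that preoperative allocation leaves patients without a time origin, or that none of these statements can coexist. Neither follows. An operation that proves non-curative still has a date, and endpoints counted from surgery are compatible with earlier allocation.
- **Ishak score.** It is not an eligibility item, and patients treated by ablation have no resected specimen. The conflict is therefore one of wording about the baseline, but it leaves the order of events unclear.
- **Table 1.** Its first column carries both an allocation and a pre-allocation label, so it is weak ground for saying that allocation is definitely preoperative. The fair conclusion is that the sections need reconciling.

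**Conclusion.** The point holds in two parts.

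The first is a weakness of the stated design. A fixed and published block of four, in an open-label single-centre trial, lets an attentive team know about 33% of assignments (about 79 of 238) and guess about 71%. The arithmetic is exact, given a team that knows the block length and follows one running list. It shows an opportunity for selection bias at entry. The documents do not show that such bias occurred, and they give no basis for its size.

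The second is an inconsistency. Table 1 places allocation before surgery, the data-collection section implies that part of the baseline comes from surgery yet precedes randomisation, and the Abstract is ambiguous. If Table 1 describes practice, some patients may prove not to meet the curative criterion after they are randomised. Their number is unknown, and the 2 to 24 rests wholly on an assumed 1% to 10%.

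The sample size is unaffected. The point should be acted on, as the change is cheap and protects the primary comparison.

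**What to change.** For all assignments still to be made:
1. Use randomly varying block sizes, for example 4/6/8, with neither the sizes nor their set disclosed to recruiting staff.
2. Have the list and envelopes held by someone outside the enrolling team, and register each patient irrevocably before the envelope is opened.

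In the protocol text:

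3. Reconcile the Abstract, Table 1, and Data collection and management so that allocation takes place after surgery and before the first postoperative study treatment. State which baseline items must be complete by then, and at what point curative treatment counts as confirmed for allocation. Table 1 marks study therapy from 0 months and the first postoperative CT at 1 month, so these entries have to be reconciled with whatever is stated.
4. If allocation stays before surgery, state that all randomised patients remain in the ITT analysis, including those whose treatment proves not to be curative.

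Cost: a new list for the remaining numbers and a few lines of protocol text. The possible imbalance at the end rises slightly, since it cannot exceed half the largest block: 2 patients with blocks of four, 4 with blocks of up to eight. Allocation is briefly delayed. Recruitment was planned to end in May 2024. If it has closed, items 1 and 2 are moot, but the timing should still be clarified and the ITT rule fixed before analysis.

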### Intervention

Participants will be equally randomized into two groups: the experimental group (postoperative antivirus strategies with switch-TDF therapy) and the controlled group (postoperative antivirus strategies with continuing-ETV therapy). TDF dosage is 300 mg per day, and ETV dosage is 0.5 mg per day.

### Follow-up

Patient follow-up begins post-hospital discharge. Visits to the surgical team will occur every 3 months during the first 3 years post-surgery. Check-ups, including CT and/or MRI, ultrasound, routine blood tests, liver and kidney function assessments, AFP, PIVKA, and HBV DNA level measurements, will be conducted at each visit (Table 1).

**Table 1 Tab1:** Participant timeline

	Study period												
	Enrollment/allocation	Post-allocation											Close-out
Timepoint	Pre-allocation	0 months	1 month	3 months	6 months	9 months	12 months	15 months	18 months	21 months	24 months	30 months	36 months
**Informed consent:**	×												
**Eligibility screen**	×												
**CT or MRI**	×												
**Laboratory test**	×												
**Allocation**	×												
**Surgery**		×											
**Interventions**													
**Post-operative switch-TDF therapy**		×	×	×	×	×	×	×	×	×	×	×	×
**Post-operative continuing-ETV therapy**		×	×	×	×	×	×	×	×	×	×	×	×
**Assessments**													
**First CT after surgery**			×										
**Regular follow-up (lab, CT or MRI)**				×	×	×	×	×	×	×	×	×	×
**Adverse events**		×	×	×	×	×	×	×	×	×	×	×	×

### Endpoints

The primary endpoint is 3-year RFS, defined as the interval from the operation to the date of the first diagnosed HCC recurrence, recorded in months. The secondary endpoint is 3-year OS, defined as the interval from surgery to death or the date of the last follow-up, recorded in months.

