### Sample size calculation

The sample size calculation was performed using the software PASS (version 2015). The parameters were obtained from our previous randomized clinical trial, which evaluated the efficacy of TDF and ETV in early-stage HBV-related HCC patients after surgery. In that study, the 3-year RFS rates were 70.4% and 82.4% for patients receiving ETV and TDF, respectively. Assuming 3-year RFS rates of 70% for the control group and 85% for the treatment group, with a one-sided alpha of 0.05 and 80% power, the corresponding sample size is 190. Accounting for a 20% dropout rate, a total of 238 patients will be included in this study.

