### Safety reporting

Both treatments’ safety will be evaluated through vital signs, physical exams, laboratory data, adverse events (AEs), and serious adverse events (SAEs). AEs encompass unexpected medical events or worsening conditions not necessarily linked to treatment, including hypophosphatemia, dizziness, diarrhea, nausea, vomiting, rash, fatigue, flatulence, and transaminase elevation. SAEs are events leading to death, life-threatening situations, hospitalization, deformities, birth defects, or significant permanent damages. AEs and SAEs will be documented in CRFs, with SAEs reported to ethics and administrative departments within 24 h.

Definition of the end of study is as follows: (1) participants have completed the last follow-up, (2) participants exhibit recurrence via imaging tests, and (3) participants die from any cause.

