### Statistical analysis

Background measures will be presented as mean ± standard deviation for continuous variables or as numbers/percentages for categorical variables. Continuous variables will be compared using a two-sided student *t*-test or Mann-Whitney *U* test, while categorical variables will undergo the chi-square test or Fisher’s exact test. Patient survival (RFS and OS) will be calculated via the Kaplan-Meier method with log-rank test. In particular, cancer-specific survival will also be calculated since decompensation serves as a competing event from HCC recurrence for death. Stage of cirrhosis, tumor burden, antiviral regimen, and other factors which may affect survival after surgery would be considered when conducting survival analysis. Generalized linear models will analyze primary and secondary endpoints. An ITT analysis, including protocol deviations, will be conducted using IBM SPSS version 26.0 software. A *p*-value < 0.05 indicates statistical significance.

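### The primary endpoint is named recurrence-free survival but counts only recurrence, so a death without recurrence is by implication censored and the reported 3-year RFS is too high

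*Protocol article*

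**What the plan says.** All places are in the protocol article.

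- **Endpoints**, primary: "The primary endpoint is 3-year RFS, defined as the interval from the operation to the date of the first diagnosed HCC recurrence". No other terminating event is named.
- **Endpoints**, secondary: "The secondary endpoint is 3-year OS, defined as the interval from surgery to death or the date of the last follow-up, recorded in months". Death enters here and not in the primary definition.
- **Safety reporting**: the conditions that end a participant's study include "participants die from any cause".
- **Data collection and management**: causes of death are to be recorded because "decompensation in patients with cirrhosis is a competing event from HCC recurrence".
- **Statistical analysis**: "Patient survival (RFS and OS) will be calculated via the Kaplan-Meier method with log-rank test". It adds that "cancer-specific survival will also be calculated since decompensation serves as a competing event from HCC recurrence for death", without naming a method for that measure. Cirrhosis stage and other prognostic factors are to be considered, and generalized linear models are mentioned for the endpoints. Neither statement changes what counts as an RFS event.
- **Mid-term analysis**: rejecting the RFS null hypothesis early may lead to the trial being discontinued.
- **Sample size calculation**: 3-year RFS is taken as 70% on ETV and 85% on TDF, tested one-sided at 0.05. The result is given as "80% power, the corresponding sample size is 190". These rates draw on an earlier trial with 3-year RFS of 70.4% (ETV) and 82.4% (TDF). The article does not say which events that trial counted.

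**The concern.** Recurrence-free survival means being alive and free of recurrence. The endpoint as defined is time to recurrence. Under Kaplan-Meier, a patient who dies first is handled as someone who could still recur later, so the curve describes recurrence in a hypothetical setting without such deaths. The percentage read off at 3 years is then neither the proportion alive without recurrence nor one minus the actual cumulative risk of recurrence.

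The protocol expects such deaths: cirrhosis is allowed at entry, and decompensation is named as competing with recurrence. A death of this kind carries no penalty for its arm in the primary comparison or in the interim decision based on it. The planning rates may also rest on a different event definition from the endpoint that is to be tested.

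**Working it through.** **1. What happens to a death without recurrence.** Three statements are read together: the primary event is recurrence only (Endpoints), the study ends for a participant who dies (Safety reporting), and the method is Kaplan-Meier with log-rank (Statistical analysis). The patient has no primary event and no later observation, which under Kaplan-Meier means censoring at death. This is implied and not written. Nowhere in the article is death an RFS event, and no competing-risk analysis of recurrence is given.

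**2. The plan's own sample size.** Inputs from Sample size calculation: p1 = 0.70, p2 = 0.85, one-sided alpha 0.05, power 80%. For two proportions with pooled variance under the null:

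n per arm = [1.645 × √(2 × 0.775 × 0.225) + 0.842 × √(0.70 × 0.30 + 0.85 × 0.15)]² / 0.15² = (0.971 + 0.489)² / 0.0225 ≈ 94.8, so 95 per arm and 190 in total. 190 / 0.80 = 237.5, so 238. Both stated figures are reproduced (power 80.1%), and this arithmetic is not in question.

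**3. Size of the overstatement.** Two assumptions that the documents do not supply are needed: (a) 70% and 85% are recurrence-only Kaplan-Meier values; (b) q, the 3-year net risk of death without recurrence, is independent of recurrence and equal in both arms. Then true RFS = S_rec × (1 − q), and the overstatement is S_rec × q.

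| Assumed q | RFS, ETV | RFS, TDF | Overstated by (ETV / TDF) | Difference |
|---|---|---|---|---|
| 2% | 0.70 × 0.98 = 68.6% | 0.85 × 0.98 = 83.3% | 1.4 / 1.7 points | 14.7 points |
| 4% | 0.70 × 0.96 = 67.2% | 0.85 × 0.96 = 81.6% | 2.8 / 3.4 points | 14.4 points |
| 6% | 0.70 × 0.94 = 65.8% | 0.85 × 0.94 = 79.9% | 4.2 / 5.1 points | 14.1 points |

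**4. Patients affected at q = 4%.** With constant hazards, the probability of dying first is h/(l + h) × (1 − RFS), where h = −ln(0.96) = 0.0408 over 3 years and l = −ln(0.70) = 0.3567 or −ln(0.85) = 0.1625.

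- ETV: 0.0408/0.3975 × 0.328 = 0.0337.
- TDF: 0.0408/0.2033 × 0.184 = 0.0369.
- With 119 per arm: 119 × (0.0337 + 0.0369) = 8.4 deaths, against about 53 recurrences. With 95 per arm it is about 6.7 deaths.

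**5. Against actual recurrence risk the error reverses.** At q = 5%, one minus the cumulative incidence of recurrence is 70.7% (ETV) and 85.4% (TDF), while Kaplan-Meier gives 70% and 85%.

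**6. Power if deaths are counted**, 95 per arm, same assumptions: 76.9% at q = 2% and 72.3% at q = 5%. The evaluable number for 80% power becomes 208 and 236 (260 and 295 after 20% dropout).

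**7. Unequal mortality.** These pairs are illustrations; nothing in the documents predicts either.

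- q = 2% ETV, 5% TDF: 0.85 × 0.95 − 0.70 × 0.98 = 80.75% − 68.6% = 12.2 points, power 61%.
- Reversed: 83.3% − 66.5% = 16.8 points, power 85%.

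**8. If the planning rates already count deaths.** True RFS is then 70% and 85%, and at q = 4% the endpoint as written would show 0.70/0.96 = 72.9% and 0.85/0.96 = 88.5%. The reported figure is again too high, and the sample size was set for a different endpoint from the one defined.

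**The case against.** The strongest reply is that the endpoint is a legitimate one under the wrong name. A log-rank test with deaths censored is a recognised comparison of cause-specific recurrence hazards, and recurrence risk is a stated aim (Aims of the study). This stands. A reader might infer that the primary test is invalid, and the documents do not support that. What fails is the label, the absolute Kaplan-Meier percentage, and any reading of the result as recurrence-free survival.

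Second, the protocol does not ignore competing risk. It records causes of death and adds cancer-specific survival for this reason. That also stands: the response is incomplete, not absent. It concerns death and leaves RFS as it was. Since no method is named for it, one cannot say that it repeats the same error.

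Third, the censoring rule is not written and may be set out in a fuller plan. That is fair for the detail. But the event definition is stated, and an analysis plan that counted deaths would depart from it.

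Fourth, the effect may be small. Entry is limited to age 18 to 70, BCLC 0 or A, Child-Pugh A and ECOG 0 or 1, so q may lie at or below the low end of the range. With equal mortality the difference moves only from 15.0 to 14.4 points at q = 4%. Excess deaths would also appear in OS and in SAE reporting, though not in the primary analysis. All of this limits the size and leaves the mismatch in place.

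**Conclusion.** The point holds in this form: the primary endpoint carries the name RFS, its definition omits death, and following it as written overstates recurrence-free survival whenever a patient dies without recurrence. The overstatement is 1.4 to 4.2 points (ETV) and 1.7 to 5.1 points (TDF) for an assumed net death risk of 2% to 6%, provided that 70% and 85% are recurrence-only rates. The documents establish neither input, so 67.2% versus 81.6% illustrates the size and should not be read as the trial's true RFS.

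A reader might also infer that the treatment comparison is biased, or that TDF is shielded from a known excess of deaths. The documents support neither. The difference barely moves under equal mortality, and no arm-specific death rate is given. What can be said is that if mortality did differ, the primary test and the interim decision would not register it.

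The correction should be made before any efficacy comparison, because it concerns the definition of the primary endpoint and costs little.

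**What to change.** - In Endpoints, define RFS as the time from operation to the first of HCC recurrence or death from any cause, and state the censoring rule for patients with neither event.
- Keep time to recurrence as a supporting endpoint, with death without recurrence as a competing event: cumulative incidence for the absolute risk, cause-specific hazards for the comparison.
- Name the method for cancer-specific survival, and treat other deaths there as competing events.
- Use the same RFS definition in the mid-term analysis.
- Establish whether the earlier trial's 70.4% and 82.4% counted deaths. If they did, the planning rates match the corrected endpoint. If they did not, restate the power or sample size with a justified rate of death without recurrence.

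The cost is wording plus one sample-size check. Deaths and their causes are already to be recorded, and a first-event endpoint needs no follow-up beyond recurrence. If the planning rates prove to be recurrence-only, the reported RFS will be somewhat lower than planned, and power at 190 evaluable patients falls below 80% by the amounts shown in the working.

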### Inclusion criteria

The inclusion criteria are as follows: (1) aged 18 to 70; (2) newly diagnosed with HBV-related HCC following clinical diagnosis criteria of the American Association for the Study of Liver Diseases (AASLD) [21]; (3) Barcelona Clinic Liver Cancer (BCLC) stage 0 or A, receiving curative liver resection or ablation; (4) ETV monotherapy for over 1 year with pre-surgery HBV-DNA load under 100 IU/mL; (5) Child-Pugh class A with or without cirrhosis, Eastern Cooperative Oncology Group (ECOG) performance status (PS) score ≤ 1; (6) appropriate renal function (serum creatinine < 124 mmol/L).

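### The primary recurrence event in this open-label trial has no diagnostic criterion, dating rule or masked call; a change of wording and of the imaging request would close most of the gap

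*Protocol article*

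**What the plan says.** All references are to the protocol article.

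- **Abstract, Background:** the study is introduced as "SWITE, a randomized, open-label, phase III trial".
- **Endpoints:** RFS is "defined as the interval from the operation to the date of the first diagnosed HCC recurrence", in months. The section gives no radiological or pathological criterion, no rule for an equivocal finding and no reader.
- **Follow-up:** "Visits to the surgical team will occur every 3 months during the first 3 years post-surgery". The content of each visit is given as "Check-ups, including CT and/or MRI, ultrasound, routine blood tests", followed by liver and kidney function, AFP, PIVKA and HBV DNA. Table 1 lists CT or MRI at each regular follow-up. Neither place gives a rule for choosing between the two.
- **Safety reporting:** one of the conditions that end a participant's study is that "participants exhibit recurrence via imaging tests".
- **Inclusion criteria:** the entry diagnosis of HCC must meet the AASLD clinical diagnosis criteria. These are attached to entry only and are not carried over to recurrence.
- **Introduction and Discussion:** the authors say that existing evidence, their own included, favours TDF over ETV for outcome after curative surgery.

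**The concern.** When the event is the date of diagnosis, it depends on a decision as well as on a finding. Take a nodule seen on the month-9 scan, judged indeterminate, and called recurrence at month 15. Under the Endpoints wording it is an event at month 15. Had it been called at once, it would have been an event at month 9. If it is never called, it is no event at all. Nothing in the definition settles which of these applies, and nothing stated keeps the person deciding from knowing the arm.

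Randomisation balances the patients but not the way in which lesions are called afterwards. If equivocal lesions were called more readily or earlier under ETV, or imaged with the more sensitive modality there, part of an RFS difference would come from assessment and not from the drug. The authors' stated expectation for TDF gives the likely direction. The same event also feeds the mid-term analysis, where rejection of the RFS null hypothesis may stop the trial.

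**Working it through.** **1. The plan's own sample size reproduces.** The inputs are in Sample size calculation: 3-year RFS 70% and 85%, one-sided alpha 0.05, power 80%. In terms of recurrence, p1 = 0.30, p2 = 0.15 and the mean is p = 0.225.

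n per arm = [1.645 × √(2p(1 − p)) + 0.842 × √(p1(1 − p1) + p2(1 − p2))]² / (p1 − p2)² = 94.8, so 95 per arm and 190 in total. With 20% dropout, 190 / 0.80 = 237.5, so 238, or 119 per arm. Both stated figures are confirmed, and this point changes neither.

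**2. What is fixed and what is left open.**

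| Element of the event | Stated? |
|---|---|
| Basis of recurrence | Imaging, by way of the end-of-study definition; not in the endpoint definition |
| Imaging schedule | Same for both arms (Follow-up and Table 1) |
| Criterion for calling a lesion | No |
| Date when a lesion is equivocal at first | No; the date is that of diagnosis |
| CT or MRI | Either, with no rule |
| Who makes the call | Not stated |
| Masking of that person | Not stated; the trial is open-label |

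One loose end concerns year 3. The Follow-up text has visits every 3 months for all 3 years, while Table 1 goes from 24 to 30 to 36 months. This applies to both arms alike, but it leaves the year-3 assessment dates less firm.

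**3. Sensitivity illustration.** The documents give no rate of equivocal lesions and no rate of differential calling, so the following rests on assumptions that are not in them: no true effect, true 3-year recurrence of 30% in both arms, a one-sided 0.05 test of the 3-year proportions, and a fraction m of TDF-arm recurrences not called by 3 years. Then p1 = 0.30, p2 = 0.30 × (1 − m), and

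P(reject) = Φ[(p1 − p2 − 1.645 × SE0) / SE1],

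where SE0 = √(2p(1 − p)/n), with p the mean of p1 and p2, and SE1 = √([p1(1 − p1) + p2(1 − p2)]/n).

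For m = 10% and n = 95: p2 = 0.27, SE0 = 0.0655, SE1 = 0.0655, (0.030 − 0.1077)/0.0655 = −1.19, so P = 11.8%. For n = 119: SE0 = 0.0585, SE1 = 0.0585, (0.030 − 0.0963)/0.0585 = −1.13, so P = 12.9%.

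| TDF-arm recurrences uncalled by 3 years | 95 per arm | 119 per arm |
|---|---|---|
| 0% | 5.0% | 5.0% |
| 5% | 7.8% | 8.2% |
| 10% | 11.8% | 12.9% |
| 20% | 23.7% | 27.3% |
| 30% | 41.2% | 47.9% |

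In patients, 10% of the expected recurrences in one arm is 0.10 × 0.30 × 95 = 2.9, or 0.10 × 0.30 × 119 = 3.6.

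**4. Delay only.** Suppose every TDF-arm call is merely late, with a constant hazard of −ln(0.70)/36 per month. Observed 3-year RFS in that arm is then 0.70^(33/36) = 0.721 for a 3-month delay and 0.70^(30/36) = 0.743 for 6 months. The same formula gives false-positive rates of 9.3% (95 per arm) and 9.9% (119 per arm) for 3 months, and 16.2% and 18.2% for 6 months. A uniform delay of this kind is an extreme case. Only equivocal lesions are realistically exposed.

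**The case against.** Much of the case on the other side stands.

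- **Article detail.** Reading procedures, rules for equivocal lesions and the wording of imaging requests often sit in a full protocol or imaging manual, which is not shown. The absence of criteria alone would not be a finding. What remains is that the endpoint rule as printed ties the event to the date of diagnosis in an open-label trial, and that a less bias-prone rule is available at almost no cost.
- **Equal schedules.** CT or MRI is planned at the same visits in both arms, so more frequent scheduled scanning of one arm is not built into the plan. This stands, and it narrows the exposure to the calling and dating of equivocal lesions and the choice of modality.
- **Endpoints against Safety reporting.** A reader might infer that the two sections contradict each other. They do not. One defines a time interval and the other says when participation ends, and a recurrence diagnosed on imaging satisfies both. For the same reason, the listing of AFP and PIVKA as check-ups does not make them event criteria.
- **Who decides.** A reader might infer that the surgical team calls recurrence, since visits are to that team. The documents do not say so. They do not say who reads the scans either.
- **Fragility of the result.** A reader might infer that two judgement calls could decide the trial. At the source-trial rates, roughly 35 against 21 recurrences of 119 give two-sided p = 0.032, and 33 against 21 give p = 0.063. That holds only for a two-sided test and a starting point chosen near the threshold. At the one-sided 0.05 used for the sample size, 33 against 21 is still significant (p = 0.032), and four calls have to go (31 against 21, p = 0.058). Any result that starts near the threshold behaves in this way, so it is no evidence of assessor bias.

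**Conclusion.** The point holds as a cheap improvement to the endpoint definition. It is not a demonstrated bias. The event and its date rest on a diagnosis with no stated criterion and no stated masking, so known allocation can influence whether and when an equivocal lesion counts, and with which modality it is seen.

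The documents do not allow the size of any effect to be derived. The figure of about 12% to 13% false positives is conditional on no true effect, 30% recurrence in both arms, a one-sided 0.05 test of 3-year proportions and 10% of TDF-arm recurrences going uncalled. It shows that three to four uncalled recurrences in one arm would be enough to matter, not that they will occur. The Statistical analysis section names the log-rank test, for which the exact figures would differ. The planned 190 and 238 are unaffected.

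**What to change.** 1. In Endpoints, define recurrence as a new lesion on contrast CT or MRI that meets the imaging criteria already cited for entry in Inclusion criteria, or histology if it is obtained.
2. Take the event and its date from the routine radiology report, and leave the antiviral assignment off the imaging request.
3. Date a lesion that is confirmed later at the first scan that showed it.
4. Word the end-of-study definition in Safety reporting to match.

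Optional: keep one modality, CT or MRI, for a given patient's trial scans.

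The cost is the endpoint wording, a short instruction to staff on imaging requests, and some retrospective re-dating of indeterminate lesions. No extra patients, scans or readers are called for, on the assumption that the scans already receive a routine radiology report. The change should be made before any comparison of RFS by arm, including the mid-term analysis.
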